# Effect of omega-3 fatty acids on TH1/TH2 polarization in individuals with high exposure to particulate matter ≤ 2.5 μm (PM2.5): a randomized, double-blind, placebo-controlled clinical study

**DOI:** 10.1186/s13063-022-06091-5

**Published:** 2022-02-24

**Keywords:** Ambient particulate matter, Omega-3 fatty acid, TH1/TH2 polarization, Immune system, Randomized controlled trial

## Abstract

**Background:**

Long-term exposure to high concentrations of PM2.5 may cause immune system dysfunction and damage to the respiratory and cardiovascular systems. PM2.5 may cause CD4 + T helper cells to polarize toward TH1 or TH2 cell types, which may be associated with the onset and progression of many human diseases. Recent studies have shown that omega-3 fatty acids can regulate human immune function and reduce physiological damage caused by air pollution; however, only limited research has examined the therapeutic effects of omega-3 fatty acids on subjects with high exposure to PM2.5 in mass transit systems such as subways.

**Methods:**

This study was designed as a prospective, randomized, double-blinded (to participants and researchers), placebo-controlled clinical trial. The research plan is to randomly select 120 eligible adults based on the difference in PM2.5 exposure in the Chengdu subway station. They should be aged 20–65 years old and work in the subway station more than or equal to 3 times a week, each time greater than or equal to 8 h, and had worked continuously in the subway station for more than 2 years. All participants will receive omega-3 fatty acids or placebo for 8 weeks. The primary outcomes will be changes in the TH1/TH2 cell polarization index and changes in serum cytokine concentrations. Secondary outcomes will be changes in early indicators of atherosclerosis, pulmonary function, COOP/WONCA charts, and scores on the Short-Form 36 Health Survey for quality of life. Results will be analyzed to evaluate differences in clinical efficacy between the two groups. A 6-month follow-up period will be used to assess the long-term value of omega-3 fatty acids for respiratory and cardiovascular disease endpoints.

**Discussion:**

We will explore the characteristics of the TH1/TH2 cell polarization index in a population with high exposure to PM2.5. Omega-3 fatty acids and placebo will be compared in many ways to test the effect on people exposed to PM2.5 subway stations. This study is expected to provide reliable evidence to support the promotion of omega-3 fatty acids in clinical practice to protect individuals who are highly exposed to PM2.5.

**Trial registration:**

Chinese Clinical Trial Registry ChiCTR2000038065. Registered on September 9, 2020

**Supplementary Information:**

The online version contains supplementary material available at 10.1186/s13063-022-06091-5.

## Background

With the rapid development of urbanization and industrialization in many countries, air pollution has become an important factor that negatively affects the health of residents in these countries [1–4]. In fact, air pollution has been identified as the cause of death for ~ 2 million people worldwide [5]. Particulate matter (PM), one of the main components of polluted air, is chemically complex and may contain biological compounds, organic compounds, and metals [5]. Studies have found that the composition of PM changes with time and space [6]. PM2.5 is a class of fine particulate matter with a diameter of < 2.5 microns. Unlike coarse PM, fine PM may reach the terminal bronchioles and alveoli of the lungs, causing oxidative stress, oxidative damage, and inflammatory reactions in epithelial cells, as well as persistent adverse effects to the human body [7–10].

The subway is a public transportation system widely used in many major cities throughout the world. As a relatively enclosed space, the PM2.5 concentration inside the subway system is several times higher than that on the street surface above [11]. PM2.5 in the subway is generated by friction between the wheels and rails, wear on the electric rails and overhead lines, electric current collectors, and arcs. PM2.5 is rich in metal elements, including iron, manganese, chromium (from rails/wheels), barium (from brakes), and copper (from electrical components) [12, 13]. Any PM2.5 that settles on the subway floor will become re-suspended in the air due to train and passenger movements, which result in a continuous circulation of PM2.5 within the subway system. Subway workers often experience long-term occupational exposure to high concentrations of PM2.5, which may lead to adverse health effects.

Located in southwestern China, Chengdu is a modern metropolis with a total population of more than 16 million. The Chengdu Metro, which has been in operation for more than 10 years, currently has 8 lines, with a total length of 358.235 km and 215 stations. In Chengdu, more than 1.4 billion commuters ride the subway each year (the Chengdu Metro Line Map is shown in Additional file 1). Previous studies have shown that short-term exposure to PM2.5 in subway systems may cause harm to humans [14]; however, few clinical studies have examined the effects of long-term exposure to PM2.5 among subway workers. To our knowledge, previous studies have mainly focused on physiological damage to humans caused by outdoor air pollution. Studies on subway employees exposed to PM2.5 are very rare. One study in China showed that the concentration of PM2.5 in the Chengdu subway was significantly higher than PM2.5 concentrations detected on city streets [15]. As the number of employees in the Chengdu subway system continues to increase, research is needed to assess potential harms that may result from PM2.5 exposure.

Omega-3 polyunsaturated fatty acids (PUFA), including eicosapentaenoic acid (EPA), docosapentaenoic acid (DPA), and docosahexaenoic acid (DHA), have been shown to produce a variety of beneficial effects on human health [16]. A large number of epidemiological studies and clinical trials have shown that consumption of omega-3 fatty acids may have beneficial effects by reducing inflammation and regulating the function of macrophages, neutrophils, T cells, and B cells [17, 18]. Studies have found that omega-3 fatty acids may regulate immune function and have beneficial health effects in clinical trials examining PM2.5 in indoor air pollution [19–21].

PM2.5 may damage the human body through systemic inflammation, changing the immune response, and increasing oxidative stress [22]. As the initial deposition site of PM2.5, airway damage includes inflammation, bronchial remodeling, and tissue fibrosis, which often appear in the early stages of disease [23]. PM2.5 exposure may disrupt the balance of TH1 and TH2 helper cells, cause the TH1/TH2 balance to shift in the direction of TH2 cells, and increase the incidence of bronchial asthma and chronic inflammatory diseases [24, 25]. Although PM2.5 exposure is known to adversely affect TH1/TH2 polarization in humans, few clinical trials evaluating the impact of omega-3 fatty acids on TH1/TH2 polarization during PM2.5 exposure have been conducted. Therefore, this study was designed as a prospective, randomized, double-blinded (to participants and researchers), placebo-controlled trial to objectively evaluate the effects of omega-3 fatty acids on TH1/TH2 polarization in subway workers exposed to PM2.5.

## Methods

### Study design

This is a randomized, single-center, placebo-controlled, double-blinded clinical trial. This research protocol complies with the standard protocol project: Interventional Trial Recommendations (SPIRIT) Guidelines (Additional Document 2). Eligible participants will be randomized 1:1 into two groups: the intervention group and the placebo group. Random numbers were generated by IBM SPSS Statistics V.25 software. The TH1/TH2 cell polarization index in the serum will be collected to determine the potential impact of people with high PM2.5 exposure. The Hospital of Chengdu University of Traditional Chinese Medicine (Sichuan Province, China) will serve as a research institution to the Chengdu Metro Company to recruit participants. The flowchart of this trial procedure is shown in Fig. 1. This study protocol has been approved by the Chinese Ethics Committee of Registering Clinical Trials (Ethical Review No.: ChiECRCT20190343). Before randomization, all eligible participants will be asked to sign an informed consent (see Additional file 3).

**Fig. 1 Fig1:**
[figure not shown]
Study flowchart

### Participant recruitment

We plan to recruit 120 participants from the Chengdu Metro Station. The recruitment methods used in this study include (1) face-to-face communication, (2) bulletin boards, and (3) posters. We will post recruitment information at various subway stations in Chengdu and broadcast the recruitment information on the subway broadcast. The members of the research team will receive uniform training after the project is launched, all of whom are medical staff with doctor certificates. The members of the research team will obtain the written consent of the participants, and their mobile phones will be kept open for 24 h to communicate with the participants at any time. Participants can enter clinical trials only after the members of the research team confirm the qualifications of the participants on the spot and sign a written informed consent form. Eligible participants will be registered and randomly assigned to placebo or omega-3 fatty acid treatment. There is no anticipated harm and compensation for trial participation. All subject personal information and trial data will be treated as confidential, which will be recorded in the individual case report forms (CRFs). These data will be uploaded in a database that only members of the research team can access. After the later data was completely uploaded, the subjects can enter the website (http://www.medresman.org.cn/login.aspx) to check. Enrollment will begin on November 1, 2020, and is expected to be completed by July 31, 2021.

### Sample size

G*Power 3.1 will be used to calculate the sample size necessary to have sufficient statistical power [26]. The sample size calculation will be based on a previous study of omega-3 fatty acids and their effects on up-regulating the TH1/TH2 ratio by ~ 32.5% [27]. The type I error is 0.05 and the power is 80%. Considering a dropout rate of 20%, we aim to recruit 120 subjects. The treatment group and the placebo group were assigned 60 participants each. Based on the grouping of our experiment, we will be divided into the high exposure group and low exposure group according to PM2.5 exposure. In the high and low exposure groups, 30 subjects were treated with omega-3 fatty acids and placebo.

### Selection criteria

Participants for this study will be recruited from long-term employees of the Chengdu subway system, who do not routinely wear professional anti-PM2.5 masks.

#### Inclusion criteria for the high PM2.5 exposure group

Employees of the Chengdu subway system, regardless of gender, 20–65 years of age, who work in one of the station halls ≥3 times per week, ≥8 h per day, and have been on the job continuously for ≥2 yearsNo obvious abnormalities detected by a physical examination in the past 1 yearHave not received hormones, antioxidant supplements (vitamin C, vitamin E), or non-steroidal anti-inflammatory drugs in the past 3 monthsNo history of surgery in the past 3 monthsWilling and mentally competent to consent to participate in this experimental study and to sign an informed consent document

#### Inclusion criteria for the low PM2.5 exposure group

Employees of the Chengdu subway system who work in offices (with an air-conditioning device equipped with PM2.5 filters), regardless of gender, 20–65 years of age, who work in the office ≥3 times per week, ≥8 h per day, and have been on the job continuously for ≥2 yearsNo obvious abnormalities detected by a physical examination in the past 1 yearHave not received hormones, antioxidant supplements (vitamin C, vitamin E), or non-steroidal anti-inflammatory drugs in the past 3 monthsNo history of surgery in the past 3 monthsWilling and mentally competent to consent to participate in this experimental study and to sign an informed consent document

#### Exclusion criteria

A long-term history of drug useRoutine use of a PM2.5 respirator that complies with China’s “PM2.5 Protective Masks” group standard (TAJ 1001-2015) during workA history of smokingA history of bleedingAn allergic reaction to flaxseed, fish, and/or seafoodA history of hepatitis, fatty liver, cirrhosis, cholecystitis, or gallstonesCurrently pregnant or lactatingParticipation in another clinical trial within the past 6 monthsInability to understand the intention of the experiment and inability to cooperate with the experimental procedure

### Randomization, allocation, and concealment

Before the subjects agree to participate in this study, all qualified subjects who satisfy the inclusion and exclusion criteria will be given an information sheet describing the study and an opportunity to ask questions and clarify their concerns with the investigators. During the study, both the participants and the researchers will be blinded to the grouping information for each subject based on the PM2.5 exposure level. According to the difference in PM2.5 exposure, 120 random numbers will be generated by BMISPSSStatistics24.0 software, and 60 random numbers will be allocated to the PM2.5 high-exposure group and PM2.5 low-exposure group (stratified random). The researcher in charge of blinding will use two opaque envelopes to seal the random numbers and will carefully check whether the serial numbers and drug numbers on the cover and letterhead are consistent with the labels on the drug packaging. Each subject will be provided with a corresponding emergency envelope. In case of an event threatening the safety of the subject, the researcher will allow the unblinding in an emergency after the evaluation so that the patient can be properly treated. In an emergency, an independent pharmacist will open the sealed envelope and notify the investigator of the assignment. Information about the date, time, and reason to remove blindness will be entered in clinical case forms (CRFs) and envelopes.

### Intervention

We plan to recruit 120 subjects who will be automatically divided into two groups based on their PM2.5 exposure level in the work environment: high PM2.5 exposure group (*n* = 60) and low PM2.5 exposure group (*n* = 60). In the high-exposure group, 30 people will receive omega-3 fatty acid treatment and the other 30 subjects will receive placebo treatment. Participants in the low-exposure group will receive an identical treatment regimen.
Intervention group: Participants will receive treatment from the same batch of omega-3 fatty acids (1200 mg/capsule) provided by Kirkland, Canada. Participants will take two capsules every morning for 8 weeks and will be followed for 24 weeks after the trial. The omega-3 fatty acid capsules will be stored in a dry environment at room temperature.Placebo group: Participants will receive placebo treatment, containing soybean oil as the main ingredient, which has been produced by the Placebo Experimental Center of the School of Pharmacy, Chengdu University of Traditional Chinese Medicine. The physical appearance and weight of the placebo will be the same as the omega-3 fatty acid capsules, and the administration methods, experimental period, and storage methods will be identical to those in the intervention group.The capsules for the intervention group and the placebo group will be packaged in the same box. Each box will contain 8 weeks of drug dosage and will include the name of the subject, dosage, consumption schedule, description of storage conditions, and expiration date. “Experiment only” will be highlighted in a prominent position on the box. We have selected soybean oil as the placebo (comparison) agent because it is commonly used in daily cooking, its physical properties are similar to omega-3 fatty acids and it has no obvious effects on TH1/TH2 polarization [28].The drug to be used in this project is a nutritional supplement with controllable safety risks. The participant may do so if he/she has no adverse events or side effects. However, if the subject has diarrhea or nausea, their participation in the trial may be suspended and the adverse event will be reported to the research team. Due to the special nature of omega-3 fatty acids, we will prohibit participants from using antioxidant supplements, such as vitamin E, during the trial. Medications used by participants to treat other diseases will not be curtailed or changed. If omega-3 fatty acids are beneficial to subjects with high PM2.5 exposure, we will put the control subjects on the “waiting list,” that is, after the trial, the control subjects will also be provided with omega-3 fatty acids for 8 weeks free of charge.

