#### Secondary outcome measures

We will evaluate the difference in secondary indicators between the treatment group and the placebo group from the following four aspects.
A pulmonary function test will be performed to evaluate the impact of PM2.5 on lung function in each subject (baseline, end of treatment, and 24 weeks).Early indicators of atherosclerosis, including IL-8 and ICAM-1, will be measured (baseline and end of treatment).The SF-36 questionnaire will be used to assess the health status of each subject and to generate a COOP/WONCA chart. The quality of life will be summarized for eight aspects: physical functioning, physical role functioning, physical pain, general health, vitality, social functioning, emotional health, and mental health (baseline, end of treatment, 12 weeks, and 24 weeks).Safety and adverse reactions to drug treatment will be monitored.

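### The allergy exclusion does not cover soybean oil, the placebo's main ingredient: a small, avoidable participant-safety gap

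*Protocol article*

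**What the plan says.** The Intervention section describes the comparator: "Participants will receive placebo treatment, containing soybean oil as the main ingredient". For the omega-3 arm the schedule is "Participants will take two capsules every morning for 8 weeks", and for placebo "the administration methods, experimental period, and storage methods will be identical to those in the intervention group". Soybean oil is chosen because "it is commonly used in daily cooking, its physical properties are similar to omega-3 fatty acids", and because it is said to have no obvious effect on TH1/TH2 polarization. Allergy is not discussed there.

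The Exclusion criteria contain one allergy item, which names flaxseed, fish and seafood. The inclusion criteria for the high- and low-exposure groups ask for an unremarkable physical examination within the past year and for no recent use of certain drugs and supplements. They do not ask about allergy.

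On allocation, Study design says "Eligible participants will be randomized 1:1 into two groups: the intervention group and the placebo group" and Sample size says "The treatment group and the placebo group were assigned 60 participants each". In the high-exposure group, "30 people will receive omega-3 fatty acid treatment and the other 30 subjects will receive placebo treatment", and the low-exposure group follows the same scheme. Under Secondary outcome measures, among the indicators to be compared between arms, the article lists "Safety and adverse reactions to drug treatment will be monitored".

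**The concern.** The protocol treats allergy to a capsule's contents as a reason to exclude someone, but its list fits the source of the active capsule only. The main ingredient of the other capsule is not on it. Read literally, the criteria admit a person who knows that they are allergic to soy and may then assign that person to daily soybean oil under blinding. At stake is an avoidable risk to a participant.

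This is not explained by the article being a condensed version of a fuller protocol. The article prints the allergy item and names its allergens, so the list can be held against the products described in the same Methods section. Eligibility is also protocol content and would not normally be left to an analysis plan.

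**Working it through.** **1. Does any printed criterion catch a soy allergy?**
- Allergy exclusion: flaxseed, fish, seafood. Soy is not named, and there is no general item on food allergy or on allergy to a study-product ingredient.
- Physical examination within the past year: this asks for no obvious abnormality, not for an allergy history.
- The remaining exclusions (drug use, respirator use, smoking, bleeding, liver and gallbladder disease, pregnancy or lactation, another trial, inability to cooperate) do not bear on it.

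A person with a known soy allergy can meet every printed criterion.

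**2. Chance of receiving the placebo.** From Sample size, 60/120 = 0.5 overall. From Intervention, 30/60 = 0.5 within each exposure group. The 1-in-2 chance follows directly from the article's own figures.

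**3. Exposure.** 2 capsules × 7 days × 8 weeks = 112 capsules per placebo participant, because the placebo schedule is the same as the active one.

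**4. How many people this could concern.** The article gives no prevalence of soy allergy, so *p* below is an assumption. Expected number on placebo = 60*p*. Chance of at least one on placebo = 1 − (1 − *p*)^60. Expected number enrolled = 120*p*.

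| Assumed *p* | Expected on placebo | Chance of at least one on placebo | Chance of none | Expected among 120 |
|---|---|---|---|---|
| 0.1% | 0.06 | 5.8% | 94.2% | 0.12 |
| 0.3% | 0.18 | 16.5% | 83.5% | 0.36 |
| 0.5% | 0.30 | 26.0% | 74.0% | 0.60 |

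As a stress test, *p* = 1% gives 0.60 expected on placebo and a 45.3% chance of at least one; *p* = 2% gives 1.20 and 70.2%. All these figures count allergic people present, not reactions. The article gives no rate of reaction to this oil.

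**5. Effect on the safety comparison.** If every soy-allergic placebo participant reacted, the expected rise in the placebo adverse-event proportion would be *p* itself: 0.1 to 0.5 percentage points over the main range, and 2 points at *p* = 2%. A single reaction, if one occurred, would move the placebo proportion by 1/60 = 1.7 percentage points. That figure is conditional on an event which, on the main range, most likely does not happen.

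**6. Effect on week-8 data.** At most 0.30 placebo participants are expected to be affected over the main range. The planned dropout allowance is 20% × 120 = 24 participants, or 12 per arm.

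**The case against.** A reader might infer that the one-sided screen tilts the safety comparison toward omega-3: people who would react to the active capsule are removed, people who would react to the placebo are kept, so soy reactions land only in the placebo arm. The documents do not support this as a claim about the results. On the assumed 0.1% to 0.5%, the likeliest number of soy-allergic placebo participants is zero. Whether this oil provokes reactions in such people is not stated. The full composition of the active capsule is not given, and the article itself calls soybean oil a common cooking oil, so exposure through diet is possible in either arm. A loss of week-8 samples large enough to matter is not supported either, as the comparison with the dropout allowance shows.

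There are also mitigating features. A soy-allergic worker may well know of the allergy and avoid the oil. Candidates receive an information sheet and can raise concerns before consenting. Team members with medical qualifications confirm eligibility on the spot. Adverse events are reported and acted on, and emergency unblinding is provided for. These lower the residual risk, but none is a criterion that keeps a soy-allergic person out. Whether the consent form names the placebo ingredient cannot be seen.

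Finally, the two sections do not contradict each other in logic; both can be followed at once. That is correct. The fault is a list that does not match the products it is meant to screen for.

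**Conclusion.** The point holds as a narrow participant-safety gap: the printed allergy exclusion omits the placebo's main ingredient, so a person with a known soy allergy is eligible and has a 1-in-2 chance of 8 weeks of daily soybean oil. This part rests only on the article's own text and allocation figures.

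The size is small and depends on an assumed prevalence. At 0.1% to 0.5%, 0.06 to 0.30 soy-allergic placebo participants are expected, with an unknown reaction rate. The effect on the arm comparison of safety is probably negligible and should not be reported as a bias. The sample size, the power and the primary comparison are untouched. Severity is minor.

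**What to change.** Bring the Exclusion criteria and Intervention sections into line, so that the allergy item covers the main ingredient of both capsules, for example by naming soybean beside the sources already listed. Put the question to each candidate at the on-the-spot eligibility check described under Participant recruitment.

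Trial status gives 31 July 2021 as the approximate completion date, before the article's publication in February 2022, so participants may already be enrolled. In that case, ask them the same question and report how many, by arm, declare a soy allergy.

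The cost is one phrase and one screening question. The downside is the loss of very few volunteers: 120*p* = 0.12 to 0.60 on the assumed prevalences. The analysis does not change.

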### Statistical methods

IBM SPSS Statistics V.25 software will be used for statistical analysis of the data collected in this study. Subjects who withdrew from the experiment but received at least one treatment will still be included in the intention-to-treat analysis. We will use various attribution methods to conduct sensitivity analysis to test whether the results are reliable for different assumptions about missing data. Demographic and baseline data will be tabulated and evaluated using analysis of variance (ANOVA) or the *χ*^2^ test. Analysis of variance was performed on categorical variables, and the Pearson *χ*^2^ test was performed on continuous variables. Subgroup analyses will be performed according to the subjects’ working years (2–6 years, 6–10 years, and over 10 years) and average working hours per week (24–36 h and over 36 h). If conditions are appropriate, subgroup analysis will be performed with reference to the above criteria. 95% CI will be used for continuous variables. In this study, all statistical tests will be two-way, and a *P* value < 0.05 is considered valid.

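### The entry and on-trial restrictions do not name non-study omega-3 or fish-oil supplements, so current users can be randomised and continue, which can shrink the omega-3 versus placebo contrast

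*Protocol article*

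**What the plan says.** **At entry.** The inclusion criteria for the high- and the low-exposure group carry the same 3-month restriction: no hormones, no antioxidant supplements (vitamins C and E are the ones named) and no NSAIDs. The exclusion criteria add a long-term history of drug use and allergy to flaxseed, fish or seafood. The allergy item concerns reactions, not intake.

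**On trial.** The Intervention section states "we will prohibit participants from using antioxidant supplements, such as vitamin E, during the trial", and then "Medications used by participants to treat other diseases will not be curtailed or changed". Hormones and NSAIDs are restricted only before entry.

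**Status of the tested agent.** The same section says "The drug to be used in this project is a nutritional supplement with controllable safety risks". It therefore uses both words, drug and supplement, for one product.

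**Sample size.** The basis is a previous study of "omega-3 fatty acids and their effects on up-regulating the TH1/TH2 ratio by ~ 32.5" per cent. "The type I error is 0.05 and the power is 80" per cent. "Considering a dropout rate of 20%, we aim to recruit 120 subjects". "The treatment group and the placebo group were assigned 60 participants each". No standard deviation is given. The Statistical methods section adds that "all statistical tests will be two-way".

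**Outcome.** The Abstract describes the primary outcomes as changes. The primary outcome section has measurements at enrolment and 8 weeks later and a comparison between arms, but does not say whether the 8-week value or the change is compared.

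**The concern.** The protocol identifies products that could interfere with the comparison and restricts them at two stages, but does not name the product that matches the intervention. A worker who already takes fish oil meets the listed product restrictions, can be allocated to either arm, and is not told to stop.

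If enough participants do so, the difference between arms in the TH1/TH2 ratio and the cytokines moves toward zero. The sample size allows for dropout and makes no allowance for this. Power would fall below the stated 80%. Since the article does not mention recording outside use, a null result would also be hard to interpret: an ineffective supplement and a comparison diluted by outside use would look alike.

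**Working it through.** **1. Does any rule cover the product?**

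| Rule | Section | Covers outside omega-3? |
|---|---|---|
| 3-month restriction: hormones, antioxidant supplements (vitamins C, E), NSAIDs | Inclusion criteria, both groups | Not named |
| Long-term drug use | Exclusion criteria | Unclear: the agent is called a nutritional supplement, and the inclusion criteria name supplements separately |
| Flaxseed, fish or seafood allergy | Exclusion criteria | No: allergy, not intake |
| Antioxidant supplements, vitamin E as example | Intervention | Not named; the class is open-ended, but its examples are vitamins |
| Instructions on capsule intake and lifestyle | Adherence | Contents not shown |

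No rule clearly bars a current user.

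**2. The stated sample size.** Evaluable total = 120 × (1 − 0.20) = 96, or 48 per arm. With no standard deviation stated, 120 can be neither confirmed nor refuted, so I solve backwards. For a two-sided test at 0.05 with 80% power,

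d = (1.960 + 0.842) × √(2/48) = 2.802 × 0.2041 = 0.572 (normal approximation); the t-test gives 0.578.

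A 32.5% effect then implies a standard deviation of 0.325 / 0.578 = 0.56, or 56% of the reference mean. This is what the stated design needs, not a figure from the documents.

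**3. How use reduces the contrast.** Let Δ be the full effect and p the share of users, equal in both arms by randomisation. Assume that outside use already gives the full effect and that the study capsules add nothing to it (the worst case).

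- *8-week values.* The omega-3 arm averages Δ and the placebo arm pΔ. Difference: (1 − p)Δ.
- *Change from baseline, stable users.* Users change by about zero in either arm. The omega-3 arm averages (1 − p)Δ and the placebo arm 0. Difference: (1 − p)Δ. Here the loss comes entirely from the omega-3 arm.
- *Change from baseline, placebo participants who start omega-3 on trial.* A starting share s raises the placebo mean by sΔ, so with no prior users the difference is (1 − s)Δ.

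Each route gives the same worst-case factor.

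**4. Power.** With the standard deviation unchanged, power = Φ[2.802 × (1 − p) − 1.960]. The t-test with d = 0.578 gives the same rounded results. To restore 80% power, n per arm = 48 / (1 − p)², rounded up, and total = 2n / 0.8.

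| Assumed p | d × (1 − p), d = 0.572 | Power | n per arm for 80% | Total with 20% dropout |
|---|---|---|---|---|
| 0 | 0.572 | 80% | 48 | 120 |
| 5% | 0.543 | 76% | 54 | 135 |
| 10% | 0.515 | 71% | 60 | 150 |
| 20% | 0.457 | 61% | 75 | 188 |

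**5. Partial blunting.** If users lose only half the contrast, the factor is 1 − p/2. With p = 20% this is 0.90, the 10% row: power 71%, not 61%. With p = 10% it is 0.95: power 76%, not 71%.

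**The case against.** **Randomisation balances background use.** It does, and so there is no systematic bias between arms from baseline use. But balance does not bring back the lost contrast.

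**The lists are not closed.** A reader might infer that the protocol sets a complete on-trial list that deliberately leaves omega-3 out. The text does not support that: vitamin E is given as an example of a class. What stands is narrower: omega-3 is not named, and it is not plainly an antioxidant supplement as the document uses the term.

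**The drug-use exclusion might catch habitual users.** The Intervention section does call the product a drug, so an investigator could apply the exclusion this way. The same sentence calls it a nutritional supplement, so different screeners could decide differently. This lessens certainty that users would enrol but does not close the gap.

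**A stable fish-oil user on placebo does not dilute a change score.** This is right, and it rules out the simplest reading, that use in the placebo arm always dilutes. Such a user has the effect at both visits and changes by about zero, like any other placebo participant. On change from baseline, the loss needs blunted response in the omega-3 arm or placebo participants who start omega-3 on trial. The placebo route applies to stable users only if 8-week values are compared.

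**The article condenses a fuller protocol.** Detailed supplement lists and case report form fields can sit there, as can the written instructions. However, the article sets out its eligibility criteria item by item and states the on-trial restriction itself, so the wording of those rules is open to comment.

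**The size is unknown.** This stands. The prevalence of use is not given, d is back-solved, and complete loss of contrast among users is a worst case.

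**Conclusion.** The point holds as a gap in the wording of the restrictions. Under the rules as written, a current omega-3 or fish-oil user can be randomised and continue, and users then contribute a reduced contrast by the routes shown above.

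The power figures of 76%, 71% and 61% for 5%, 10% and 20% use bound the loss. They assume 48 evaluable per arm, exactly 80% power without outside use, an unchanged standard deviation and no contrast at all from users. If use is rare or blunting partial, the loss is small.

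A reader might go further and infer that the trial is contaminated, that its result is biased between arms, or that 120 is the wrong sample size. The documents support none of these. They give no evidence of actual use, the expected effect of balanced use is dilution rather than bias, and 120 cannot be checked without a standard deviation. The point warrants a change because the remedy is cheap, not because material loss has been shown.

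**What to change.** 1. Name omega-3 and fish-oil supplements in the 3-month entry criterion for both exposure groups and in the on-trial restriction in the Intervention section.
2. For participants already enrolled, record baseline omega-3 supplement use on the case report form, without knowledge of allocation.
3. Pre-specify a sensitivity analysis of the primary outcome that excludes baseline users. Use before randomisation cannot be affected by allocation, so this exclusion introduces no post-randomisation selection. It does not deal with participants who start omega-3 during the trial.

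The cost is one phrase in three places, one screening question and a slightly smaller eligible pool. Timing matters: the article gives recruitment from November 2020 with completion expected around July 2021, and was published in February 2022. The entry wording may therefore come too late, leaving steps 2 and 3, with baseline use then resting on recall.
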